## Abstract

Vitamin D insufficiency remains common in adults, and supplementation with cholecalciferol (vitamin D_3_) is widely used to improve circulating 25-hydroxyvitamin D [25(OH)D]. At the same time, circular-economy strategies are increasingly applied to nutraceutical production, including the valorization of fish processing by-products as sources of lipid-soluble bioactives. However, clinical evidence directly comparing fish processing by-product-derived vitamin D_3_ with conventional synthetic vitamin D_3_ at commonly used nutritional doses remains limited. D-FISH is a single-center, randomized, double-blind, parallel-group, non-inferiority trial enrolling adults aged 18–60 years with a baseline plasma of 25(OH)D 20–40 ng/mL. Participants will be randomized (1:1) to receive either fish processing by-product-derived or synthetic vitamin D_3_ at the same nutritional dose (600 IU once daily with the evening meal) for 12 weeks. The primary endpoint is the between-group difference in the change in plasma 25(OH)D from day 0 to day 84, assessed against a pre-specified non-inferiority margin of 5 ng/mL, with analyses conducted in full analysis and per-protocol populations. Secondary endpoints include markers of mineral metabolism (calcium, phosphorus, PTH), fasting lipid profile, anthropometrics, and tolerability/safety outcomes; early 25(OH)D kinetics will be explored at 72 h, day 7, and day 28. The study will inform biochemical non-inferiority and short-term tolerability but is not powered to evaluate clinical outcomes (NCT07127796).

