### 2.11. Sample Size Determination

The planned sample size is 48 participants (24 per group). The calculation is based on a non-inferiority framework for the primary endpoint, assuming a standard deviation of 5.5 ng/mL for the change in 25(OH)D, a non-inferiority margin of 5 ng/mL, 90% power, and an allowance for approximately 10% drop-out and exclusions due to non-compliance. The non-inferiority margin (5 ng/mL, ~12.5 nmol/L) was prespecified to represent a conservative and clinically acceptable difference in biochemical response between formulations at nutritional doses while preserving feasibility for this proof-of-concept trial. Although no universally accepted minimal clinically important difference for 25(OH)D change exists, the margin was selected a priori to avoid differences likely to be regarded as meaningful in routine biochemical monitoring.

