### 2.12. Statistical Analysis Plan

Analyses will be conducted in predefined analysis populations: a full analysis set (FAS; intention-to-treat principle), a per-protocol (PP) set excluding major protocol deviations, and a safety set including all participants who receive at least one dose of study treatment.

For the primary endpoint, non-inferiority of fish-derived vitamin D_3_ versus synthetic vitamin D_3_ will be concluded if the lower bound of the confidence interval for the between-group difference (fish-derived minus synthetic) in the change in 25(OH)D at week 12 is above −5 ng/mL. A repeated-measures ANCOVA model will be used, with treatment group and visit as factors and baseline 25(OH)D as a covariate. The primary analysis will be performed in the FAS and repeated in the PP set as a sensitivity analysis.

Secondary continuous outcomes will be analyzed using ANCOVA models with treatment group as factor and baseline value as covariate (or appropriate non-parametric alternatives if model assumptions are not met). Categorical outcomes (e.g., AE incidence) will be summarized as counts and percentages and compared using appropriate tests where relevant. As an exploratory sensitivity analysis, the month/season of blood sampling may be included as a covariate to assess the robustness of the primary comparison. No interim analysis is planned.

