The choice of a non-inferiority framework is particularly appropriate in this setting, where the investigational product is not primarily expected to outperform the standard comparator but rather to provide comparable biological benefit while potentially offering advantages in sustainability, sourcing, and production. Non-inferiority trials have become a major tool in modern clinical research when an effective standard exists and placebo-controlled comparisons would be unethical or uninformative; their original rationale was to identify “good substitutes” that preserve efficacy while improving other attributes such as convenience, safety, or cost [32]. At the same time, non-inferiority designs require careful methodological execution and interpretation, given their complex assumptions and the potential for design or reporting features to bias inference toward concluding non-inferiority [33,34]. Evidence from the high-impact cardiovascular literature highlights that non-inferiority trials have historically varied widely in margin selection and frequently presented methodological or reporting limitations—particularly when results were not consistently reported across intention-to-treat and per-protocol/as-treated analyses [35,36]. Against this backdrop, D-FISH incorporates key safeguards to strengthen interpretability, including a prespecified non-inferiority margin and confirmation of the primary analysis in both full analysis and per-protocol populations. The selected margin was defined a priori to represent a conservative difference in 25(OH)D change that would be unlikely to be regarded as clinically meaningful in routine biochemical monitoring, thereby supporting a more robust inference even in the presence of potential deviations that could dilute between-group contrasts [34,35].

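### Section 2.12 lets non-inferiority be declared on the FAS alone, so it does not deliver the confirmation in both analysis sets that the Discussion presents as a safeguard

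*Protocol article*

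**What the plan says.** Section 2.12 gives one success criterion. Non-inferiority "will be concluded if the lower bound of the confidence interval for the between-group difference (fish-derived minus synthetic") in the 12-week change lies above −5 ng/mL. That sentence names no analysis set. The set is fixed at the end of the same paragraph: "The primary analysis will be performed in the FAS and repeated in the PP set as a sensitivity analysis". The section defines the second set as "a per-protocol (PP) set excluding major protocol deviations".

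The Discussion describes the design differently. It first criticises published non-inferiority trials for weak methods or reporting, "particularly when results were not consistently reported across intention-to-treat and per-protocol/as-treated analyses". It then names, as one of the trial's own safeguards, "confirmation of the primary analysis in both full analysis and per-protocol populations".

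The Abstract is neutral: "with analyses conducted in full analysis and per-protocol populations", with no ranking of the sets and no joint rule. Section 2.11 sizes the trial with "an allowance for approximately 10% drop-out and exclusions due to non-compliance". The article does not say what follows if the two sets disagree.

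**The concern.** A sensitivity analysis that cannot change the conclusion does not confirm it. If the lower limit clears −5 ng/mL in the FAS but not in the PP set, section 2.12 allows a claim of non-inferiority although the safeguard named in the Discussion has failed.

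This matters in a non-inferiority trial because missed capsules or off-study vitamin D, when similar in both arms, tend to pull the arms together and so favour the claim. The design leaves room for this. Capsules are counted only at the end-of-study visit (sections 2.5.3 and 2.9), outside vitamin D is controlled by instruction (section 2.9), and participants who stop the product are encouraged to complete the final assessments (section 2.10), so they can contribute to the FAS.

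The point does not depend on an unseen analysis plan. The article itself assigns the PP set its role in section 2.12 and credits it with a larger one in the Discussion.

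**Working it through.** **Inputs from section 2.11.** SD of change 5.5 ng/mL, margin 5 ng/mL, power 90%, 24 per group (48 in total), about 10% allowance. Alpha and the confidence level are not stated, so one-sided 0.025 and 0.05 are both shown.

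**Step 1: the plan's own sample size.** n per arm = 2 × [5.5 × (z₁₋α + z₀.₉₀) / 5]², with a true difference of 0.
- One-sided 0.05: 2 × [5.5 × (1.645 + 1.282) / 5]² = 20.7, so 21. 21 / 0.9 = 23.3, so 24 per arm and 48 in total. This reproduces the plan.
- One-sided 0.025: 2 × [5.5 × (1.960 + 1.282) / 5]² = 25.4, so 26. 26 / 0.9 = 28.9, so 29 per arm and 58 in total. This does not.

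**Step 2: false non-inferiority when the FAS decides alone.** Assumptions, none of them from the documents: the true difference is −5 ng/mL in adherent participants and 0 in unexposed ones, the unexposed fraction q is the same in both arms, and FAS data are complete. A two-sample t lower limit on change stands in for the repeated-measures model.

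The expected FAS difference is −5 × (1 − q). A noncentral t calculation with SD held at 5.5 and 24 per arm gives:

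| q | FAS difference | one-sided 2.5% | one-sided 5% |
|---|---|---|---|
| 5% | −4.75 | 3.6% | 6.8% |
| 10% | −4.5 | 4.9% | 9.1% |
| 20% | −4.0 | 9.0% | 15.3% |

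Holding the SD at 5.5 makes these slightly high, because mixing exposed and unexposed participants widens the spread. A simulation of 100,000 trials with whole participants (2 or 5 of 24 per arm unexposed, PP set nested in the FAS) allows for this:

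| Unexposed per arm | One-sided alpha | FAS alone | Both sets |
|---|---|---|---|
| 2 of 24 | 2.5% | 4.0% | 2.2% |
| 5 of 24 | 2.5% | 8.3% | 2.3% |
| 2 of 24 | 5% | 7.9% | 4.6% |
| 5 of 24 | 5% | 14.7% | 4.7% |

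Repeat runs move these by about 0.2 percentage points at most.

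**Step 3: power cost of requiring both sets.** True difference 0, exclusions unrelated to outcome, same simulation:

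| PP per arm | One-sided alpha | FAS | PP | Both | FAS passes, PP fails |
|---|---|---|---|---|---|
| 22 | 5% | 92.8% | 90.7% | 89.7% | 3.0% |
| 19 | 5% | 92.7% | 86.4% | 85.3% | 7.4% |
| 22 | 2.5% | 86.8% | 83.7% | 82.3% | 4.5% |
| 19 | 2.5% | 86.8% | 77.6% | 76.0% | 10.9% |

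The last column shows that discordant results are not rare even when the products are truly equivalent. The plan needs a stated reading for them in any case.

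**The case against.** **Only section 2.12 sets a success criterion.** A reader might infer that the article contains two rival formal decision rules. It does not: the Discussion is descriptive prose, and an FAS analysis repeated in the PP set could loosely be called confirmation in both. This stands. What remains is that the Discussion claims a protection that the rule does not supply.

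**The PP set is not protected by randomisation.** Its exclusions can bias the difference in either direction, so the FAS is usually, but not always, the lenient set. This stands too. It is a reason against relying on PP alone, not against requiring both.

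**The size is constructed.** The deficit sits exactly at the margin, every unexposed participant shows no difference, and 20% is twice the plan's allowance. That allowance also covers drop-outs, who may have no day-84 value and so need not dilute the FAS. Moreover, false is judged here against the adherent-only difference; under an intention-to-treat reading, a true FAS difference of −4.5 or −4.0 ng/mL lies inside the margin. All of this holds, so the figures are an illustration and not an estimate of the trial's error rate.

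**The trial was not shown to be sized for the PP set.** Section 2.11 allows for non-compliance exclusions, which makes that inference tempting, but it names no analysis set. Joint power is below 90% in every scenario above.

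**Conclusion.** The point holds as a mismatch between the rule and the claim made for it. Under section 2.12, an FAS success is enough and a PP failure changes nothing, so the safeguard described in the Discussion is not in force.

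Under the stated assumptions, false non-inferiority on the FAS alone is roughly 1.6 to 3.3 times the nominal level (4.0 / 2.5 = 1.6; 8.3 / 2.5 = 3.3; 7.9 / 5 = 1.6; 14.7 / 5 = 2.9). Requiring both sets brings it back to slightly below nominal. With less non-adherence the excess is smaller. The documents do not support reading these figures as the error rate to expect in this trial. The mismatch itself rests on the text alone and needs none of the assumptions. It should be corrected before unblinding.

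**What to change.** In section 2.12, state that non-inferiority is concluded only if the lower confidence limit exceeds −5 ng/mL in both the FAS and the PP set, and that discordant results are reported as inconclusive. Delete the words that label the PP repeat a sensitivity analysis.

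The edit is about one sentence, but it is not free. With about 10% excluded, power is just under 90% at one-sided 5% and about 82% at one-sided 2.5%. With about 20% excluded, it is about 85% and 76%. The sponsor should accept that loss knowingly.

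The alternative is to keep the FAS-only rule. The Discussion must then stop presenting confirmation in both sets as a safeguard and call the PP analysis supportive, and the article should say how a discordant PP result will be read. That removes the mismatch at no cost in power, but it also gives up the protection.

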### 2.13. Data Management and Confidentiality

Study data will be recorded in a study-specific electronic case report form (eCRF) hosted on REDCap-Unibo, with role-based access control, individual authentication, and full audit trails to ensure traceability of data entry and modifications. Data handling will follow the ICH-GCP principles and applicable data protection requirements [29,30]. Participants will be identified in the database by a unique study code, and any direct identifiers will be kept separate from research data whenever applicable, with access restricted to authorized study personnel. Data quality and integrity will be supported by predefined validation rules and structured data fields, together with quality control procedures including range and logic checks, query generation and resolution, and periodic review of completeness and internal consistency. Data exports for analysis will be performed in a controlled manner, limiting access to pseudonymized datasets. Study records will be stored securely and retained/archived according to institutional policies and applicable regulations, ensuring confidentiality, controlled access, and data availability for monitoring and verification activities where required.

### 2.14. Ethics and Dissemination

The trial will be conducted in accordance with the principles of the Declaration of Helsinki [31] and ICH-GCP [29]. The study protocol has been submitted for review to the Comitato Etico Area Vasta Emilia Centro (AVEC), and all required institutional authorizations will be obtained prior to participant recruitment. Written informed consent will be obtained before any study-related procedure.

Study findings will be disseminated through peer-reviewed publication and presentation at scientific conferences, irrespective of the study outcomes. The trial has been registered on ClinicalTrials.gov (identifier NCT07127796) [27].

### 2.15. AI Use Acknowledgement

The graphical abstract of this paper was created using Google Collaboratory (Google Notebook). ChatGPT 5.2 was used exclusively for language editing purposes. The same will be done with the final report of the study.

## 3. Discussion

D-FISH addresses a timely question with combined clinical and sustainability relevance: whether a vitamin D_3_ supplement derived from fish processing by-products (valorization of materials otherwise discarded) can achieve improvements in plasma 25(OH)D that are not clinically meaningfully lower than those obtained with a conventional synthetic vitamin D_3_ comparator when administered at an equivalent nutritional dose. Importantly, D-FISH is designed to test biochemical non-inferiority in 25(OH)D response and is not powered to evaluate clinical outcomes; therefore, no conclusions regarding clinical benefit can be drawn from this trial. If non-inferiority is demonstrated, the trial will provide an evidence-based rationale for considering circular-economy approaches to vitamin D nutraceutical production while preserving expected biological efficacy—a paradigm that is increasingly relevant as nutraceutical development expands beyond efficacy alone to include broader value dimensions.

Nevertheless, the primary endpoint is clinically meaningful. In routine practice, 25(OH)D is the accepted biomarker used to diagnose suboptimal vitamin D status and to guide supplementation strategies, monitoring, and dose adjustment. In this context, demonstrating non-inferior biochemical repletion represents a necessary translational prerequisite before considering broader implementation or investing in larger outcome-driven trials. Moreover, direct randomized, double-blind head-to-head comparisons between by-product-derived and synthetic vitamin D_3_ formulations at nutritional doses remain scarce, despite growing interest in sustainable sourcing and production pathways.

The choice of a non-inferiority framework is particularly appropriate in this setting, where the investigational product is not primarily expected to outperform the standard comparator but rather to provide comparable biological benefit while potentially offering advantages in sustainability, sourcing, and production. Non-inferiority trials have become a major tool in modern clinical research when an effective standard exists and placebo-controlled comparisons would be unethical or uninformative; their original rationale was to identify “good substitutes” that preserve efficacy while improving other attributes such as convenience, safety, or cost [32]. At the same time, non-inferiority designs require careful methodological execution and interpretation, given their complex assumptions and the potential for design or reporting features to bias inference toward concluding non-inferiority [33,34]. Evidence from the high-impact cardiovascular literature highlights that non-inferiority trials have historically varied widely in margin selection and frequently presented methodological or reporting limitations—particularly when results were not consistently reported across intention-to-treat and per-protocol/as-treated analyses [35,36]. Against this backdrop, D-FISH incorporates key safeguards to strengthen interpretability, including a prespecified non-inferiority margin and confirmation of the primary analysis in both full analysis and per-protocol populations. The selected margin was defined a priori to represent a conservative difference in 25(OH)D change that would be unlikely to be regarded as clinically meaningful in routine biochemical monitoring, thereby supporting a more robust inference even in the presence of potential deviations that could dilute between-group contrasts [34,35].

Several additional design features further support interpretability. The randomized, double-blind, parallel-group structure reduces selection and ascertainment biases and supports unbiased outcome assessment. The primary endpoint—change in 25(OH)D from baseline to week 12—directly captures the intended biological effect of supplementation and aligns with real-world practice, where 25(OH)D remains the standard biomarker used to evaluate vitamin D status. Importantly, the investigational formulation is supported by a structured upstream workflow, including controlled raw material handling, supercritical CO_2_ extraction, analytical characterization and standardization, and microencapsulation, together with a dedicated safety testing program addressing relevant contaminants. From a translational standpoint, this quality-by-design and traceability approach is a non-trivial component of sustainability-oriented nutraceutical development, as it helps ensure that environmental advantages do not come at the expense of reproducibility, standardization, or safety.

The intermediate sampling time points (72 h, day 7, and day 28) represent an additional asset. Although the study is not designed for mechanistic modelling of absorption, distribution, or compartmental kinetics, these early measurements provide a pragmatic description of short-term 25(OH)D response under daily administration. This may help contextualize potential differences in response trajectories between formulations that differ in source matrix and processing and may generate hypotheses for future research aimed at clarifying determinants of early response patterns under nutritional-dose supplementation.

Limitations should also be acknowledged. The trial is single-center and is powered for a biochemical non-inferiority endpoint rather than clinical outcomes; thus, no conclusions regarding patient-relevant benefit can be drawn. The 12-week duration—while appropriate for capturing meaningful changes in 25(OH)D at nutritional doses—does not inform longer-term maintenance, seasonal variability, or downstream endpoints. Moreover, eligibility criteria restrict enrolment to adults aged 18–60 years with baseline 25(OH)D 20–40 ng/mL, which supports homogeneity but limits generalizability to older adults, individuals with more severe deficiency, or those with major comorbidities. In addition, the trial does not formally control for or adjust analyses by individual sunlight exposure, seasonal variability, dietary vitamin D intake, or body composition, which may contribute to between-individual variability in 25(OH)D response. As a consequence, seasonal fluctuations and day-to-day variability in UVB exposure may influence individual trajectories in 25(OH)D despite randomization. Finally, since the protocol includes a fixed evening-meal administration schedule, the trial is not designed to evaluate whether different circadian timing strategies may influence tolerability or biochemical response. Moreover, although tolerability and safety are systematically assessed, the sample size and follow-up are insufficient to draw definitive conclusions regarding rare or longer-term adverse events, and safety findings should be interpreted as short-term tolerability signals.

In conclusion, D-FISH is a randomized, double-blind non-inferiority trial designed to evaluate whether a fish processing by-product-derived vitamin D_3_ formulation produces a change in 25(OH)D that is not clinically meaningfully lower than a synthetic comparator at the same nutritional dose. The study will inform short-term biochemical efficacy and tolerability, but it is not powered to assess clinical outcomes or establish interchangeability. Larger multicenter, longer-term, outcome-driven trials will be required before any broad clinical adoption can be considered.

## Figures and Tables

**Figure 1 jcm-15-01186-f001:**
[figure not shown]
Study flow diagram of the D-FISH trial. After screening and informed consent, eligible participants are randomized 1:1 to receive fish processing by-product-derived or synthetic vitamin D_3_ (600 IU/day) for 12 weeks (one capsule daily with the evening meal). Assessments are performed at day 0, day 3 (72 h), day 7, day 28, and day 84. Adverse events are collected throughout follow-up.

**Table 1 jcm-15-01186-t001:** Eligibility criteria.

Section	Criteria
Inclusion criteria	(1) Men or women aged 18–60 years (2) Plasma 25(OH)D between 20 and 40 ng/mL (3) Ability to understand study procedures and comply with trial requirements (4) Written informed consent provided prior to any study-related procedure
Exclusion criteria	(1) Current intake of vitamin D-containing supplements or medications (2) Osteopenia/osteoporosis, rheumatologic diseases, or history of non-traumatic fractures (3) Known hyperparathyroidism, hypercalcemia, or severe renal failure (eGFR < 30 mL/min/1.73 m^2^) (4) Known fish allergy/intolerance or allergy to fish-derived products (5) Preventive drug treatments (e.g., lipid-lowering or antihypertensive agents) not stable in type and dose for ≥3 months (6) Pregnancy or lactation (7) Any condition likely to compromise adherence to the protocol (including clinically relevant malabsorption syndromes)

25(OH)D, 25-hydroxyvitamin D; eGFR, estimated glomerular filtration rate.

**Table 2 jcm-15-01186-t002:** SPIRIT (Standard Protocol Items: Recommendations for Interventional Trials) schedule of enrolment, interventions, and assessments for the D-FISH trial.

Procedures/Assessments	Enrolment/ Baseline (Day 0)	72 h (±1 Day)	Day 7 (±1 Day)	Day 28 (±3 Days)	End of Study (Day 84 ± 5 Days)
Informed consent	X				
Eligibility assessment	X				
Randomization (1:1)	X				
Dispense study product	X				
Study product intake (daily, 600 IU/day)	X	X	X	X	X
Concomitant therapies review	X				X
Vital signs	X				X
Anthropometrics (weight, height, waist, hip; BMI)	X ^†^				X ^‡^
Adverse events assessment	X	X ^§^	X ^§^	X ^§^	X
Tolerability/acceptability interview					X
Pill count/accountability					X
Blood sampling: 25(OH)D	X	X	X	X	X
Blood sampling: calcium, phosphorus, PTH	X				X
Blood sampling: lipid profile (TC, LDL-C, HDL-C, TG)	X				X

^†^ baseline anthropometrics include also height for BMI calculation; ^‡^ end-of-study anthropometrics include weight and circumferences, BMI will be recalculated; ^§^ brief AE/tolerability check may be performed during intermediate sampling, according to site logistics. Abbreviations: 25(OH)D, 25-hydroxyvitamin D; AE, adverse event; BMI, body mass index; HDL-C, high-density lipoprotein cholesterol; LDL-C, low-density lipoprotein cholesterol; PTH, parathyroid hormone; TC, total cholesterol; TG, triglycerides.

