#### 2.8.2. Secondary Endpoints

Secondary endpoints are intended to characterize biological correlations of vitamin D repletion, as well as the overall tolerability and safety profile of the interventions. Changes from baseline to week 12 will be assessed for key markers of mineral metabolism, including plasma calcium, phosphorus, and parathyroid hormone (PTH). In addition, given the clinical context and the interest in potential cardiometabolic correlates, changes will be evaluated in the fasting lipid profile—total cholesterol, LDL-C, HDL-C, and TG. These measures are included as exploratory cardiometabolic correlates and to exclude clinically relevant adverse shifts, acknowledging that evidence on vitamin D-related lipid effects is mixed across cholesterol fractions and more consistent for TG. Changes will also be assessed in anthropometric measures, including body weight, waist and hip circumferences, and BMI.

Tolerability and acceptability will be captured through structured participant assessment/interview as specified in the protocol, alongside systematic collection of adverse events throughout follow-up. Safety outcomes include the incidence of adverse events and serious adverse events, withdrawals due to adverse events, and clinically relevant changes in vital signs.

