### 2.10. Safety Monitoring and Adverse Events

Adverse events (AEs) will be collected from the time of informed consent until the end-of-study visit. AEs will be captured through spontaneous participant reporting as well as through structured assessment at each study contact, including targeted questioning and review of concomitant medications and clinically relevant findings. Any sleep-related complaints potentially occurring during supplementation (e.g., insomnia or changes in perceived sleep quality) will be recorded as part of the adverse event assessment. Each AE will be documented with onset and resolution dates, severity (e.g., mild/moderate/severe), outcome, and any action taken regarding the study intervention. All events will be evaluated for seriousness and for their potential relationship to the study product based on clinical judgement and temporal plausibility. Serious adverse events (SAEs) will be managed, documented, and reported in accordance with institutional procedures and applicable regulatory requirements, with timely communication to the appropriate oversight bodies when indicated. Participants may discontinue the intervention at any time without prejudice. Criteria for withdrawal include participant request, unacceptable intolerance, intercurrent conditions requiring discontinuation, protocol deviations that may compromise safety, or safety concerns at the investigator’s discretion. Where feasible, participants who discontinue the intervention will be encouraged to complete end-of-study assessments, and all AEs will be followed until resolution, stabilization, or a clinically acceptable outcome.

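### Section 2.10 requires structured adverse-event questioning and medication review at every contact, but Table 2 makes the three interim adverse-event checks optional and marks no medication review at them

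*Protocol article*

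**What the plan says.** Section 2.10 fixes the collection period: "Adverse events (AEs) will be collected from the time of informed consent until the end-of-study visit". Besides spontaneous reporting, it requires "structured assessment at each study contact, including targeted questioning and review of concomitant medications and clinically relevant findings". Section 2.8.2 describes the same activity as "systematic collection of adverse events throughout follow-up" and names the outcomes that depend on it: "Safety outcomes include the incidence of adverse events and serious adverse events, withdrawals due to adverse events, and clinically relevant changes in vital signs".

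The legend of Figure 1 sets out the contacts: "Assessments are performed at day 0, day 3 (72 h), day 7, day 28, and day 84". Table 2 schedules blood sampling for 25(OH)D at all five.

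Table 2 marks AE assessment at all five contacts, but the marks at 72 h, day 7 and day 28 carry a footnote: "brief AE/tolerability check may be performed during intermediate sampling, according to site logistics". The row "Concomitant therapies review" is marked at day 0 and day 84 only, with no footnote.

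Section 2.7 presents Table 2 as the summary of assessment timing, and Section 2.8.3 refers all endpoints to it. Section 2.9 forbids starting vitamin D products during the study, says that changes in background therapy will be recorded systematically, and uses the deviation log to define the per-protocol (PP) set before database lock.

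**The concern.** The article states two rules for the same contacts. One is mandatory and structured; the other is brief and discretionary. A site working from the text and a site working from the schedule would collect different data, and the article itself directs endpoint assessment to the schedule.

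Two uses of the data are affected. AE incidence is a named safety outcome, and short-term tolerability is one of the things the trial says it will inform. If interim questioning is left to convenience, a mild event that resolves in the first weeks may be recorded for a participant who was asked and lost for one who was not. Sleep complaints, which Section 2.10 singles out for recording, are the kind of event that may not be volunteered or remembered twelve weeks later.

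The second use is deviation recording. A new vitamin D product is a prohibited event that a medication review is meant to find. With the review scheduled only at the two ends, an early start has to be recalled at day 84 or reported unprompted, and its start date becomes less certain.

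**Working it through.** No reported figure is at issue, so the check compares the two rules contact by contact. Inputs: Section 2.10, the contact days in the Figure 1 legend, and the rows, visit windows and footnote of Table 2.

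| Contact | AE questioning, Section 2.10 | AE questioning, Table 2 | Medication review, Section 2.10 | Medication review, Table 2 |
|---|---|---|---|---|
| Day 0 | due | due | due | marked |
| 72 h | due | optional | due | not marked |
| Day 7 | due | optional | due | not marked |
| Day 28 | due | optional | due | not marked |
| Day 84 | due | due | due | marked |

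**Counts.** Under Section 2.10 each task is due at 5 of 5 contacts, or 4 of 4 after baseline. Under Table 2 AE questioning is unconditional at 2 of 5 (1 of 4 after baseline) and optional at 3. Medication review is marked at 2 of 5 (1 of 4 after baseline) and absent at 3.

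**Period covered by one assured assessment.** Under Table 2, the first assured structured questioning after baseline is at day 84 ± 5, so the look-back is 84 days nominally and 79 to 89 days across the window.

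**What mandatory interim checks would change.** The look-back periods become 3, 7 − 3 = 4, 28 − 7 = 21 and 84 − 28 = 56 days, which sum to 84. The last gap is 56/84 = 67% of follow-up. With the windows of ±3 and ±5 days it runs from 79 − 31 = 48 to 89 − 25 = 64 days. The gain is therefore prompt ascertainment over the first 28 days (28/84 = 33% of follow-up); the later period is unchanged.

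**Does any other text resolve the conflict?** The Figure 1 legend says that AEs are collected throughout follow-up, but not whether interim checks are obligatory. Section 2.9 has participants reminded at each contact to report missed doses, which is not an AE question or a medication review. Its promise to record therapy changes systematically names no contact at which this is done. None of these settles which rule governs the interim visits.

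**The case against.** The strongest reply has five parts.

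- **Medication review may be part of the AE assessment.** Section 2.10 lists it as a component, and the AE row has a mark at all five contacts. The separate row could then be a formal start-and-end review. This reading is possible, but it does not rescue the interim contacts, because the footnote makes the whole interim AE check optional and any review inside it would be optional too.
- **Other capture routes exist.** Spontaneous reports are accepted from consent to end of study, and AE assessment, medication review, interview and pill count are all scheduled without condition at day 84. This stands: capture is weakened, not absent, and a discretionary check may in practice always be done.
- **The article is condensed.** A fuller protocol may settle visit procedures. However, the point is a conflict between two rules that the article itself states, not a missing detail.
- **No bias by arm follows.** A reader might infer that uneven collection distorts the AE comparison. With one center and blinded participants and assessors, the documents offer no mechanism for ascertainment to differ by arm. The likelier result is under-recording that varies between participants or visits. This objection stands.
- **No bias toward non-inferiority follows.** A reader might also infer that undetected vitamin D use corrupts the PP set and pulls the primary contrast toward non-inferiority. The documents do not support that step. Deviations are classified after the day-84 review and before database lock, so late detection is still in time, and misclassification would need a failure of recall or reporting as well. The primary analysis is in the full analysis set, where off-protocol use affects the contrast whether or not it is detected. This objection stands too.

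**Conclusion.** The contradiction is established on the face of the article and nothing in it resolves the matter. For the three interim contacts, Section 2.10 and Table 2 give incompatible instructions on AE questioning, and Table 2 marks no medication review. The size is 3 of 4 post-baseline contacts, with one assured structured assessment over 84 days if the table is followed literally.

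The consequence is limited: mild or transient AEs and early starts of prohibited vitamin D products could be under-recorded, or recorded unevenly between participants, and left to day-84 recall or spontaneous report. This assumes that staff follow Table 2, as Section 2.8.3 directs for endpoints, and that at least some optional checks are skipped. How many would be skipped, and how many events lost, cannot be estimated from the document. It is worth correcting before data collection, because the trial presents its tolerability data as systematically collected.

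**What to change.** Reconcile Table 2 with Section 2.10:

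1. Replace the discretionary footnote with a mandatory structured AE check at 72 h, day 7 and day 28, using the same question set for every participant.
2. Mark concomitant-therapy review at those three contacts, with an explicit question on new vitamin D products and their start dates.
3. Add the matching eCRF fields, so that a check with no events can be told apart from a check not done.

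**Cost.** A table edit, the eCRF fields and a few minutes at visits that participants already attend for blood sampling. With 48 planned participants this is at most 48 × 3 = 144 short checks.

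**What it leaves open.** Day 28 to day 84 would still depend on the final visit and spontaneous reports, and the article should say so when it calls AE collection systematic.
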